## Abstract

**Background:**

Schizophrenia is one of the most burdensome psychiatric disorders. Novel neuromodulatory techniques including cathodal transcranial direct current stimulation (c-tDCS) and continuous theta burst stimulation (cTBS) using repetitive transcranial magnetic stimulation (rTMS) are increasingly being used in alleviating the auditory verbal hallucinations that are persisting despite adequate antipsychotic treatment. Brain connectivity modulation by stimulating the left temporoparietal junction is thought to mediate these effects. The differential neurobiological mechanisms and efficacy of these two neuromodulation techniques are not known. We are unaware of any systematic studies that can guide clinicians in choosing between the two techniques. This protocol describes a parallel-arm, double-blind, randomized cross-over study to identify resting brain functional connectivity markers of response to cTBS and c-tDCS persistent auditory hallucinations to improve the efficacy of interventions.

**Methods:**

Two hundred and ten consenting patients with schizophrenia with persistent auditory hallucinations will be randomly assigned to receive 15 days (30 sessions) of c-tDCS+sham-TBS or sham-tDCS+cTBS over the left temporoparietal region at three study centres. After a gap of 2-4 weeks, non-responders to the intervention will cross-over to the other arm. Clinical assessments, neurocognitive assessments, and multimodal investigations (magnetic resonance imaging, electroencephalography, heart rate variability, investigative transcranial magnetic stimulation-transcranial direct current stimulation, gene polymorphisms) will be conducted at baseline and repeated after the end of both phases of the trial. A differential pre-treatment resting brain functional connectivity signal will identify responders to cTBS or c-tDCS.

**Registration:**

Clinical Trial Registry of India (
CTRI/2021/05/033783) registered on 25/05/2021.

## Introduction

### Background rationale for the study

Schizophrenia is a complex neuropsychiatric disorder characterized by delusions, hallucinations, disorganized behaviour, and progressive cognitive deficits. This disorder is ranked among the top ten disabling medical disorders by the World Health Organization (
Collaborators, 2022). Despite the best available treatments, about 25 – 35% of patients with schizophrenia show partial or no clinical improvement (
Siskind *et al.*, 2017). Residual or persisting symptoms contribute to a critical component of the disability burden. In addition, most of the existing antipsychotic medications are associated with intolerable side effects as well.

Contextually, alternative paradigms involving neuromodulatory techniques are gaining increasing attention in the treatment of schizophrenia. Transcranial Direct Current Stimulation (tDCS) has been reported to help treat hallucinations resistant to antipsychotic treatment in patients with schizophrenia (
Bose *et al.*, 2018;
Fregni *et al.*, 2021). tDCS is a non-invasive neuromodulatory technique that delivers low-intensity, direct current to cortical areas through the surface application of electrodes on the scalp, facilitating or inhibiting spontaneous neuronal activity (
Gowda *et al.*, 2019). Alternatively, several transcranial magnetic stimulation (TMS) paradigms have also been investigated for persistent auditory hallucinations. rTMS non-invasively administers repeated magnetic stimuli through the scalp to the underlying cortical regions to induce action potentials in these cortical neurons. Theta burst stimulation (TBS) is a well-tolerated resource-sparing protocol of TMS in which bursts of magnetic pulses are delivered in a short time. Uninterrupted bursts of magnetic pulses, as administered in Continuous TBS (cTBS), are known to induce long-term depression and reduce the excitability of the cortical neurons. cTBS is a safe and well-tolerated treatment option for auditory hallucinations when applied unilaterally (
Nieuwdorp *et al.*, 2015) as well as bilaterally (
Lefaucheur *et al.*, 2020;
Tyagi *et al.*, 2022).

Auditory verbal hallucinations (AVH) are one of the most common symptoms in schizophrenia (
McCarthy-Jones *et al.*, 2017) and are specific target of interest with these neuromodulatory techniques. AVH are a major cause of distress and burden to patients with an increased risk of self-harm, suicide, violence or homicide (
Dugré & West, 2019;
Kjelby *et al.*, 2015). A significant proportion of patients respond to antipsychotics but may persist in having distressing AVH even during the first episode of schizophrenia (
Sinkeviciute *et al.*, 2021). Even though the neuromodulatory effects of either TMS or tDCS have been investigated in many clinical conditions, there are only a few reported clinical trials in pain disorders in which these two interventions were compared head-to-head (
Andre-Obadia *et al.*, 2023;
Bonifácio de Assis *et al.*, 2022;
Forogh *et al.*, 2021). However, we are unaware of any published work that has compared cTBS and cathodal tDCS, both of which are known to have a modulatory effect on the temporoparietal junction (TPJ) in reducing hallucinations. The modulation of connectivity of brain networks is poised to be one of the major mechanisms mediating the alleviation of auditory hallucinations with both tDCS (
Mondino *et al.*, 2016;
Paul *et al.*, 2022;
Zhuo *et al.*, 2021) and cTBS. At present, there is no research study that informs whether a patient with schizophrenia may differentially respond to one of these two treatments (i.e. cTBS and cathodal tDCS); such information can be vital in expediting appropriate neuromodulation treatment choices. This research project addresses this compelling research question.

### Aims and hypothesis

**
*Primary*
**

To identify resting brain functional connectivity markers of response to continuous Theta Burst Stimulation (cTBS) and cathodal transcranial Direct Current Stimulation (c-tDCS) in patients with schizophrenia with persistent auditory hallucinations to improve the efficacy of interventions.Hypothesis: A differential pre-treatment resting brain functional connectivity signal will identify responders to cTBS or c-tDCS

**
*Secondary*
**

To compare the neurobiological profile of patients with schizophrenia with persistent auditory hallucinations with matched healthy controls using multi-modal data [brain imaging, Electroencephalography (EEG), TMS-tDCS perturbation study metrics, Heart Rate Variability (HRV), and neuroplastic gene polymorphisms].To examine the differential effect of cTBS versus c-tDCS on the neurobiological profile of patients with schizophrenia with persistent auditory hallucinations using multi-modal data (brain imaging, EEG, TMS-tDCS perturbation study metrics, HRV) and potential interactions with neuroplasticity gene polymorphisms.To evaluate the predictive utility of multi-modal data (brain imaging, EEG, TMS-tDCS perturbation study metrics, HRV, and neuroplastic gene polymorphisms) in identifying clinical response to cTBS or c-tDCS in patients with schizophrenia with persistent auditory hallucinations.

This study protocol adheres to the SPIRIT guidelines (
[name] *et al.*, 2023) and the example consent form and study proforma can be found as
*Extended data* (
[name] *et al.*, 2023).

### Participants

**
*Trial design*
**

We employ a parallel-arm double-blinded randomized cross-over design with an allocation ratio of 1:1 to identify the differential pre-treatment resting-state functional connectivity marker of response to cTBS and cathodal tDCS in persistent auditory hallucinations in schizophrenia.

**
*Study setting*
**

This would be a hospital-based study. The study would be conducted on patients with persistent auditory hallucinations at three mental health care and research institutes in India- National Institute of Mental Health and Neurosciences (NIMHANS), Bengaluru; Central Institute of Psychiatry (CIP), Ranchi; and Kasturba Medical College (KMC), Manipal. The study would be centrally coordinated at NIMHANS.

### Selection of patients

Patients with schizophrenia (as per the selection criteria listed below) will be screened and recruited for this research study from the clinical services of the three participating institutes.

**
*Inclusion criteria*
**

1. Diagnosis of Schizophrenia spectrum and other psychotic disorders (DSM-5) (
APA, 2013);2. Age 18–60 years;3. Any sex;4. Right-Handedness [Edinburgh Handedness Inventory] (
Oldfield, 1971);5. Persistence of auditory hallucinations without remission despite treatment with at least one antipsychotic medication at an adequate dose for a minimum period of six weeks. Non-remission of auditory hallucinations is defined with a score of moderate or high (>2) on the Global Rating of Hallucinations in the scale for the assessment of positive symptoms (
Andreasen, 1984). Individuals who may have had received electroconvulsive therapy would also be included.6. Capacity to consent for research studies as per the assessment using the University of California, San Diego Brief Assessment of Capacity to Consent (UBACC) (
Jeste *et al.*, 2007)7. Written informed consent.

**
*Exclusion criteria*
**

1. Suicidal risk necessitating electroconvulsive therapy / any other psychiatric emergency2. Score of > 6 on Calgary Depression Rating Scale Addington (
Addington *et al.*, 1994)3. Pregnancy / Post-Partum state (within 6 months of childbirth) (
Chauhan & Tadi, 2022)4. Substance use disorder in the last six months (except caffeine or nicotine)5. Comorbid neurological/medical disease that can affect the brain structure/function6. Any Contraindication for Magnetic Resonance Imaging (like metallic implants, claustrophobia)7. Any Contraindication for Transcranial Magnetic Stimulation (assessed using TMS adult safety screen (
Keel *et al.*, 2001)8. Any Contraindication for Transcranial Direct Current Stimulation

### Interventions

Participants would be randomised to receive either “cTBS with sham-tDCS” or “active tDCS with sham TBS.” The stimulation will be administered after localising the left TPJ based on the anatomical localisation method using T1-weighted MRI, wherever available. The MR image in the Anterior Commissure-Posterior commissure (AC-PC) plane would be 3D reconstructed. The junction where the left Sylvian fissure takes an upward and/or backward turn would be identified. An imaginary plane would be drawn in the coronal section cutting across this junction. The deepest point on the superior temporal sulcus in this imaginary coronal plane would be the target point for stimulation (
Dollfus *et al.*, 2018). When the T1-Weighted MR image is unavailable, the junction between anterior 1/4th and posterior 3/4th in an imaginary line drawn joining T3 and P3 located using 10–20 EEG system will be considered left TPJ for targeting the stimulations. The electric field modelling of the TMS and tDCS is provided in
Figure 1.

**Figure 1. f1:**
[figure not shown]
Demonstrates the simulated magnitude of the local electric field rTMS (using a standard Cool-B-70 coil for dI/dT of 66A/uSeconds) (on the left side) and conventional tDCS (for the parameters as described in the stimulation protocol above) (on the right side) for targeting persistent auditory hallucinations in patients with schizophrenia. The simulations were performed using SimNIBS ver 4.1 (
https://simnibs.github.io/) on the MNI-152 brain template. The colour gradient indicates the local magnitude of the electric field (magnE) in Volts/meter.

**
*Continuous Theta Burst Stimulation (cTBS) with sham tDCS*
**

cTBS will be delivered to the left temporoparietal junction (TPJ) as triplet 50 Hz bursts, repeated at 5-Hz (given every 200 ms); in a continuous train of 40 s, repeated thrice at intervals of 5 min for a total of 1800 pulses per session; at 120%RMT. Neuronavigated-TMS would be administered for cTBS wherever available.

Sham tDCS would be administered using a cathode placed over the left TPJ and an anode placed over the left dorsolateral prefrontal cortex (DLPFC). The left DLPFC would be identified as the scalp location midway between F3 (determined using Beam F3 software) and Fp1 of 10–20 EEG system. Conductible rubber electrodes would be placed inside 0.9 mmol saline wetted 5×7cm pouches (
https://soterixmedical.com/) for delivering tDCS. In sham stimulation, a direct current would be administered with 20 seconds of fade-in incrementing to 2mA intensity, followed by 20 seconds of fade-out phase. There will be no current delivery during the rest of the 20-minute duration.

**
*c-tDCS + Sham-TBS*
**

In active tDCS, the electrode placement and stimulation parameters for sham-tDCS would be maintained as mentioned above. A 2mA current will be delivered for 20 minutes with 20 seconds each of fade-in and fade-out periods (
Bose *et al.*, 2018).

For sham TBS - intermediate theta-burst stimulation paradigm (im-TBS) would be administered using the targeting protocol as mentioned for cTBS. The im-TBS bursts would consist of 5-s theta burst trains repeated every 15 s (ie.,10 seconds inter-train interval) (
Bagali *et al.*, 2023). A train of 225 pulses (35 secs) will be repeated thrice every 5 mins. Two such sessions will be delivered each day, spaced across at least 3 hours. The im-TBS protocol has little effect on the underlying cortical excitability (
Bagali *et al.*, 2023) and has been used as a sham protocol in previous TBS clinical trials (
Kohutova *et al.*, 2017). Since true TMS pulses will be delivered, the risk of participant bias will be minimal.

Two such sessions will be delivered each day, spaced across at least 3 hours for 15 days for a total of 30 sessions. The TBS and tDCS (active or sham) will be delivered one after the other in the same order for a given subject throughout the course of the intervention. The order of TBS and tDCS will be altered in consecutive subjects at each site.

Adherence to intervention

All sessions would be provided at the hospital by a team of researchers. The financial burden on the participants would be mitigated by covering the incidental expenses and reasonable compensation for their time and other costs. Adverse effects would be diligently monitored, and any discomfort to participants would be addressed. In case of intolerance to TBS, the highest tolerable dose below 120%RMT will be administered. The research subject will have easy access to the team of investigators to clarify any study-related queries. These measures would enhance intervention adherence and study retention.

Concomitant care

In case of any deviation from the study guidelines due to unforeseen situations, the same would be documented and reported. Participants with a change in antipsychotic dose of more than 25% from the dose at the initiation of the intervention or a change in the antipsychotic medication or other neuromodulatory interventions would be considered drop-outs. All ongoing psychotropic medications and psychosocial interventions would be allowed to be concomitant with the study intervention. No new interventions would be initiated during the study.

Outcome

The primary outcome measure would be a differential change in the resting-state functional brain connectivity after “cTBS+sham tDCS” vs “active tDCS+ im-TBS”. Functional MRI will be acquired at baseline and after the end of each step of the intervention. Identifying the resting state markers would partake seed-based connectivity approach around the stimulation-targeted as well as other hallucination related brain region including fronto-temporo-parietal opercular regions, insula, angular gyrus, hippocampus and parahippocampal gyri. (
Jardri *et al.*, 2011b;
Kühn & Gallinat, 2012;
Rollins *et al.*, 2019;
Thomas *et al.*, 2016;
van Lutterveld *et al.*, 2013;
Zmigrod *et al.*, 2016)

Secondary outcome measures include broader clinical symptoms, adverse effects, and neurobiological parameters (The detailed protocol of neurobiological parameters will be described in a separate paper). Clinical symptoms would be measured by the auditory hallucinations rating scale (AHRS) (
Haddock *et al.*, 1999), Scale for assessment of positive symptoms (SAPS) and negative symptoms (SANS) (
Andreasen, 1983;
Andreasen, 1984), Calgary Depression Scale for Schizophrenia (CDSS) (
Addington *et al.*, 1994), Clinical Global Impressions (CGI) and Montreal Cognitive Assessment (MoCA) (
Nasreddine *et al.*, 2005) will be applied at baseline and every week till the end of the intervention. Cognitive and functional abilities will be assessed using the Brief Assessment of Cognition in Schizophrenia (BACS) (
Keefe *et al.*, 2004), Groningen Social Disability Schedule (GSDS) (
Wiersma *et al.*, 1988) and social and occupational functioning scale (SOFAS) (
Morosini *et al.*, 2000) at baseline and after each step of intervention.

Safety of the intervention sessions will be another secondary outcome measure: the tDCS-related adverse effect questionnaire Field (
Brunoni *et al.*, 2011;
Chhabra *et al.*, 2020) and the TMS-related adverse effects questionnaire Field (
Giustiniani *et al.*, 2022) will be used to monitor adverse effects after each intervention session.

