### Participant timeline

Step1: Patients meeting the selection criteria would be approached to participate in the study. A written informed consent would be obtained as approved by the ethics committees, after describing the study procedures with video aids. All treatments would be added to ongoing pharmacotherapy. In step-1, Participants would be randomised to either of the groups to receive “cTBS with sham-tDCS” or “active tDCS with sham TBS” twice a day for 15 days (over 3 weeks).

Step-2:

Upon non-response to step-1, participants would cross over to the other set of interventions in step-2 after a wash-out period of 2–4 weeks. Participants with <30% improvement in AHRS from baseline at the end of 2–4 weeks of the trial would be considered non-responders for inclusion to Step-2. Written informed consent would again be obtained before the initiation of step 2.

The order of TBS and tDCS would be maintained as was delivered in step-1 for the given participant (See
Figure 2).

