**Figure 2. f2:**
[figure not shown]
Depiction of the study procedure. In the first step of the study, the patients with persistent auditory verbal hallucinations would be randomized to receive 15 days of cTBS+sham-tDCS or sham TBS+active tDCS. Patients with clinical non-response even after 2–4 weeks of the end of the trial will be cross-covered to receive 15 days of the other set of interventions. Neuroimaging, and neurophysiological tests would be done before initiating and after the end of intervention with each step. Blood samples would be collected for genetic polymorphism assays at the baseline. Blue stars depict the time points of symptom rating and multimodal data acquisition. SZ: Schizophrenia, tDCS: transcranial direct current stimulation, cTBS: continuous theta burst stimulation, TMS: Transcranial Magnetic Stimulation, MRI: Magnetic resonance imaging, EEG: Electroencephalogram, TMS/tDCS: Transcranial magnetic stimulation/transcranial direct current stimulation, BDNF: Brain-derived neurotrophic factor, COMT: Catechol-O-methyltransferase.

**
*Sample size*
**

In order to identify a clinically relevant and appropriately corrected statistically significant signal from resting-state brain connectivity data with sufficient (~80%) power to differentiate (P<0.05) groups of responders and non-responders, a sample size ranging from 27 to 32 has been recommended for each group (
Pajula & Tohka, 2016;
Thirion *et al.*, 2007;
Zandbelt *et al.*, 2008) and similar sample size has shown utility in studies attempting to predict response (
Khalili-Mahani *et al.*, 2017;
Martens *et al.*, 2022;
Parlikar *et al.*, 2023;
Zhang *et al.*, 2022). Keeping with this, we will recruit 210 participants who will be randomized in part-1 of the treatment. Anticipating ~15% dropout, we will have ~180 participants who will complete the part-1 treatment. Assuming a third of the participants respond to either treatment arm, a sample of 60 and 120 will be categorised as responders and non-responders, respectively. We expect at least three-quarters of the non-responders to consent to the crossover treatment. Given our experience in a previous trial (

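### The named primary outcome (between-arm change in connectivity) does not test the primary hypothesis (baseline connectivity identifies responders) and should be realigned with it

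*Protocol article*

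**What the plan says.** The primary hypothesis under Aims and hypothesis reads: "A differential pre-treatment resting brain functional connectivity signal will identify responders to cTBS or c-tDCS". The Trial design paragraph gives the same purpose, "to identify the differential pre-treatment resting-state functional connectivity marker of response to cTBS and cathodal tDCS", and the Methods part of the abstract repeats the hypothesis.

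The Outcome paragraph under Interventions then says: "The primary outcome measure would be a differential change in the resting-state functional brain connectivity after" cTBS with sham tDCS versus active tDCS with im-TBS. The rest of that paragraph gives the scan times and the seed regions. It does not link connectivity to response.

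Four other places bear on the point:
- **Secondary aims.** The second one is to examine the differential effect of the two treatments on neurobiological measures, brain imaging included.
- **Secondary outcomes.** AHRS, the scale that defines response, is listed here.
- **Sample size.** It is argued from "power to differentiate (P<0.05) groups of responders and non-responders".
- **Data analysis plan.** It labels prediction of clinical outcome from resting-state fMRI features as the primary objective.

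**The concern.** The hypothesis has baseline connectivity as predictor, clinical response as outcome, and a predictor effect that differs by treatment. The named primary outcome contains none of these. It asks whether the two treatments move connectivity by different amounts.

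The two questions are separable. The treatments may shift connectivity differently while baseline connectivity says nothing about who improves, and the reverse is equally possible. Followed as written, the primary outcome could be positive with no evidence for the hypothesis, or negative when the hypothesis is true.

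This is not detail that an article leaves to a fuller document. The article states both the primary hypothesis and the primary outcome, and an analysis plan could not follow both as primary.

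**Working it through.** **Passages side by side**

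| Place in the protocol article | Role of connectivity | Role of clinical response |
|---|---|---|
| Primary hypothesis; Trial design; abstract | baseline predictor | outcome |
| Outcome paragraph (primary) | post-baseline change, compared between arms | none |
| Second secondary aim | changed by treatment, compared between arms | none |
| Sample size | signal that separates groups | defines the groups |
| Data analysis plan, prediction phase | predictor | outcome |

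The primary outcome sits with the secondary aim. The other places concern response.

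**Reproducing the plan's sample-size figures**
- Completers: 210 × 0.85 = 178.5, given as about 180.
- Responders: 180 / 3 = 60. Non-responders: 180 − 60 = 120.
- Crossing over: 0.75 × 120 = 90.
- Responders per arm at 1:1: 60 / 2 = 30. Non-responders per arm: 120 / 2 = 60.

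The chain reproduces. It sizes a responder contrast, not the named primary outcome.

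**Smallest difference detectable with 80% power**

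The inputs are a two-sided 5% level (the protocol gives 5% without sidedness), 80% power, the step-1 completers above, one uncorrected test and the normal approximation. The multiplier is 1.960 + 0.842 = 2.802.
- Named primary outcome, 90 v 90: 2.802 × √(2/90) = 0.42 SD.
- Pooled responders v non-responders, 60 v 120: 2.802 × √(1/60 + 1/120) = 0.44 SD.
- Difference between arms in the responder/non-responder contrast on baseline connectivity, cells 30/60/30/60: 2.802 × √(1/30 + 1/60 + 1/30 + 1/60) = 2.802 × √0.1 = 0.89 SD.

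At an illustrative 0.5 SD, power is 92% for the first contrast and 35% for the third.

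**Can the two targets come apart?**

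This was checked in 2,000 simulated trials per scenario, with 90 completers per arm and response odds of 0.5 (one third) at average baseline connectivity. The effect sizes are assumptions, because the protocol gives none.
- True arm difference in change of 0.5 SD, no predictive baseline signal: the named primary outcome is significant in 91% of trials, the arm-by-response test in 5%.
- No arm difference in change, baseline connectivity predicting response in opposite directions by arm (log-odds slopes of ±0.6 per SD): the named primary outcome is significant in 5.5%, the arm-by-response test in 95.5%.

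**The case against.** The strongest reply is that nearly everything else in the protocol serves one aim. The abstract, hypothesis, trial design, sample size and analysis plan all concern connectivity markers of response. The sample-size section promises models for general and treatment-specific response signals. The analysis plan has a prediction phase built on resting-state fMRI, and baseline scans and AHRS ratings are scheduled. This stands, and it limits the point in three ways.

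- A reader might infer that the trial cannot answer its question. The documents do not support that, because the analysis and the data are both planned.
- A reader might see three rival primary questions, with the team free to choose among them after the data are seen. That goes too far. Comparing responders with non-responders is one way to find a marker of response, so the sample-size contrast serves the stated aim. The text out of line is the primary-outcome statement.
- A reader might say that all the candidate tests differ greatly in sensitivity. They do not: 0.42 and 0.44 SD are almost equal, and only the differential contrast stands apart.

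The 0.89 SD figure also rests on choices the protocol does not make: a binary response, one uncorrected test and step 1 only. About 90 participants are expected to be treated again in step 2, and they are not counted in it.

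None of this removes the mismatch. A prediction analysis planned elsewhere does not make the named primary outcome a test of the hypothesis.

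**Conclusion.** The primary outcome is wrong as written. It contradicts the primary hypothesis and the trial-design statement, matches a secondary aim, and disagrees with both the sample-size contrast and the analysis plan's primary objective. That conclusion rests on the text alone and needs no effect size.

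The numbers show what realignment brings into view. Under the plan's own assumptions, the differential contrast needs about 0.89 SD for 80% power, roughly twice the 0.42 SD for the arm comparison now named.

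A reader might go on to infer that the trial is shown to be underpowered for its hypothesis. The documents do not settle that. They state no effect size, so power at any given SD is illustrative, and a continuous outcome or use of step-2 data could change the figure.

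**What to change.** 1. Make clinical response on AHRS in step 1 the primary outcome, with baseline connectivity as predictor and a baseline-connectivity-by-arm test for the differential hypothesis.
2. Move the between-arm change in connectivity to the secondary aim that already covers it.
3. State one time point for response. Participant timeline says "Participants with <30% improvement in AHRS from baseline at the end of 2–4 weeks of the trial would be considered non-responders", while the Figure 2 legend places the 2–4 weeks after the end of the trial. These passages must be reconciled; which one is right is for the investigators.
4. Align the sample-size section with the chosen contrast, and state its sensitivity (about 0.89 SD under the assumptions above) with those assumptions.

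Restating the primary aim and hypothesis as a mechanistic comparison of the treatments would also remove the contradiction. It would, however, give up the question that the abstract, design, sample size and analysis plan are built around.

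The cost is an amendment to the wording of the protocol and, where it carries the same primary outcome, the registry entry. No new data, visits or patients are needed. The downside is that the stated sensitivity for the differential hypothesis becomes less favourable than the present text suggests.
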